## Abstract

**Introduction::**

Allergic rhinitis (AR) is an immunoglobulin E (Ig E)-mediated inflammatory disease. Intranasal phototherapy is a promising treatment modality because it has a profound immunosuppressive effect, but the available evidence of its use for AR is insufficient. Therefore, rigorously designed randomized controlled trials (RCTs) are needed. Our objective is to describe the protocol for a feasibility trial to assess the effects and safety of intranasal phototherapy for the treatment of AR.

**Methods and analysis::**

This is a study protocol for a single-center, randomized, double-blind, parallel, placebo-controlled, investigator-initiated pilot study. A total of 40 patients with AR will be randomly assigned to the medical device or sham device group in a 1:1 ratio. The participants will receive intranasal phototherapy with a medical or sham device for 20 min 5 times a week for 2 weeks. The primary outcome will be the mean change in the Total Nasal Symptom Score (TNSS) from baseline to 2 weeks. The secondary outcomes will include the Rhinoconjunctivitis Quality of Life Questionnaire (RQLQ) score, Nasal Endoscopy Index, total serum Ig E level, and eosinophil count.

**Discussion::**

The findings of this study will provide the basis for subsequent large-scale definitive RCTs to confirm the effects and safety of intranasal phototherapy for the treatment of nasal symptoms in patients with AR who do not respond well to conventional therapy. This study may assist in the development of noninvasive treatment for patients with AR.

**Trial registration::**

This study was registered at the Korean National Clinical Trial Registry, Clinical Research Information Service (KCT0003253).

## Introduction

1

Allergic rhinitis (AR) is an inflammatory disease of the nasal membranes that results from an immunoglobulin E (Ig E)-mediated immune reaction to allergen exposure.^[1]^ The major symptoms of AR are nasal congestion, rhinorrhea, nasal itching, and sneezing.

AR is a common respiratory disease that affects 10% to 30% of the global population.^[2,3]^ AR affects 10% of the pediatric population and 10% to 15% of the adolescent population in Korea, and it has been reported that the prevalence of persistent AR has increased over the last decade.^[4]^

AR might not be associated with severe morbidity and mortality. However, it has been reported that patients with AR often have poor quality of life (QOL). AR disrupts sleeping, interrupts learning, and reduces productivity at work.^[5]^ Moreover, AR is associated with asthma, rhinosinusitis, conjunctivitis, and chronic cough.^[6]^

For the management of AR, allergen avoidance and medication such as antihistamines, nasal decongestants, and corticosteroids are recommended as conventional therapies.^[7]^ However, avoiding allergens completely is almost impossible for most people.^[8]^ Also, there are risks of adverse effects with long-term use of medications such as rhinitis medicamentosa.^[9]^ Additionally, there are some patients whose symptoms do not improve completely even with these medications and who have some limitations and special considerations for using these medications, such as patients who are pregnant or breastfeeding.^[10]^

For these reasons, the use of less conventional treatments is particularly prevalent in patients with AR.^[11,12]^ Additionally, it was reported that more than 50% of patients with AR used multiple therapies.^[13]^ Recent studies are underway to develop new treatment options for AR patients.

As phototherapy might reduce the number of eosinophils,^[14]^ induce apoptosis of immune cells and inhibit the reaction of inflammatory mediators,^[15]^ it has been suggested that intranasal phototherapy might be effective in relieving the symptoms of AR.^[16,17]^

However, there is one comparative pilot study in Korea, and it did not include a control group.^[18]^ Thus, it is necessary to perform studies to establish evidence and assess the clinical applicability of intranasal phototherapy.

We designed a single-center, randomized, double-blind, parallel, placebo-controlled, investigator-initiated, pilot study to validate the effects and safety of intranasal phototherapy for AR.

## Methods

2

### Objective

2.1

The aim of this study is to describe the protocol for a randomized controlled trial designed to clinically assess the effects and safety of intranasal phototherapy for AR in comparison with those of a sham device.

### Study design and setting

2.2

This is a double-blind, randomized, placebo-controlled, parallel-group, single-center, investigator-initiated, and pilot study. This study will be conducted at the Woosuk Korean Medicine Medical Center, Jeonju, Republic of Korea.

A total of 40 participants will be recruited for this trial and will be randomly allocated to two parallel groups: the medical device group or the sham device group. The trial will consist of a 2-week intervention period and a 1-week follow-up period. In the intervention period, 10 sessions of treatment will be conducted. The study design is summarized in Figure 1 and Table 1. The study protocol (version 1.2) was developed as required by the Standard Protocol Items: Recommendations for Interventional Trials (SPIRIT) guidelines (Additional file 1).

**Figure 1 F1:**
[figure not shown]
Flowchart of this study.

**Table 1 T1:**
[figure not shown]
Schedule of enrolment, interventions, and assessments.

### Recruitment

2.3

The trial will be advertised on the hospital bulletin board, outside the clinics of each center, and the website of the universities, which are located within geographical proximity to the hospital area. The posters will contain brief descriptions and outline the purpose of this study, the inclusion criteria, and the intervention. Written informed consent will be obtained from all study participants before enrolment, and all participants have the right to participate or withdraw from the study at any time without penalty.

### Participant inclusion and exclusion criteria

2.4

#### Inclusion criteria

2.4.1

Participants will be included in this study if they meet all of the following criteria:

1.Aged ≥19 years2.Presence of two or more symptoms of AR (nasal congestion, rhinorrhea, nasal itching, and sneezing)3.Positive reaction to an allergen in the multiple allergen simultaneous test (MAST)4.Voluntary participation in this study and signing of the patient consent form after explanation of the purpose of the study.

#### Exclusion criteria

2.4.2

Participants will be excluded if they meet any of the following conditions:

1.Current use of any of the following medications or inability to stop taking medication that is unsuitable for this clinical trial (however, enrolment in this trial is possible after the suggested minimum wash-out period before Visit 2).(a)Use of antihistamines/H1 blockers within the previous week(b)Use of corticosteroids (intranasal) within the previous 2 weeks(c)Use of corticosteroids (systemic) within the previous 30 days(d)Use of anticholinergics within the previous week(e)Use of leukotriene receptor antagonists within the previous 4 weeks(f)Use of decongestants within the previous 3 days(g)Use of tricyclic antidepressants or phenothiazines within the previous 2 weeks(h)Use of non-steroidal analgesics within the previous 2 weeks(i)Use of other inappropriate medications as judged by the investigator2.Use of traditional Korean medicine treatments (herbal medicine, acupuncture, moxibustion, cupping, etc) to treat AR within the previous 2 weeks3.Use of laser therapy to treat AR within the previous 2 weeks4.Diagnosis of malignant neoplasm, anemia, active pulmonary tuberculosis, infection, or other severe systemic disease5.Presence of anatomical obstructions or deformities of the nasal cavity or nasal surgery within the previous 6 months6.Past history of active respiratory disease such as asthma7.Hypertension or diabetes8.Treatment with immunotherapy or systemic corticosteroid therapy within the previous 2 years9.Hypersensitivity reactions to phototherapy or from taking related drugs10.Presence of a scar on the irradiation spot11.Pregnant, planning a pregnancy or breast-feeding12.Participation in other clinical trials within the previous 1 month13.Difficulty enrolling in this trial or receiving treatment14.Others: ineligible for participation as judged by the investigator

### Intervention

2.5

Participants will be randomly assigned to two groups: an experimental group (medical device that emits low-level laser light) and a control group (sham device that emits LED light) at a ratio of 1:1. Participants will receive phototherapy in each nasal cavity for 20 min, 5 times a week for 2 weeks.

The medical device that will be used is the Wellrhino unit (Optowell Co., Ltd., Jeonju-Si, Korea), which emits a low-level laser light consisting of two wavelengths, 670 and 830 nm, with unique sounds; the sham device emits LED light at 650 nm. Both devices will be identical in appearance and characteristics.

Participants will not be allowed to use medications related to AR or therapeutic interventions such as acupuncture and herbal prescriptions for AR during the trial period.

### Outcome measures

2.6

#### Primary outcome

2.6.1

The primary outcome is the change in the Total Nasal Symptom Score (TNSS) from baseline to 2 weeks. The TNSS assesses 4 nasal symptoms (nasal congestion, rhinorrhea, nasal itching, and sneezing) on a five-point scale: 0, no symptoms; 1, mild; 2, moderate; 3, severe; and 4, very severe.^[19]^ TNSS will be measured at every visit, and we will analyze the differences in effects between groups.

#### Secondary outcomes

2.6.2

The secondary outcomes include changes in Rhinoconjunctivitis Quality of Life Questionnaire (RQLQ) score, Nasal Endoscopy Index, total serum IgE level, and eosinophil count level. The RQLQ is an instrument used to assess rhinoconjunctivitis-related QOL and daily activities, which contains 28 items in 7 domains (activity limitation, sleep problems, nose symptoms, eye symptoms, non-nose/eye symptoms, practical problems, and emotional function).^[18,20]^ The RQLQ score will be assessed twice: just prior to the start of the treatment at visit 2 and at the end of the treatment at visit 11.

The Nasal Endoscopy Index assesses nasal cavity conditions according to 4 aspects: color (pale or hyperemia), dryness or dampness, rhinorrhea, atrophy, or edema.^[21]^

The Nasal Endoscopy Index will be evaluated at every visit. The instrument used is the KAZAMA ENT treatment unit (KAU-3000 HARMONY, ENT Co., Ltd., Incheon, Republic of Korea).

We will also examine the total serum IgE level and eosinophil count at screening (visit 1) and visit 11 to evaluate the effects of intranasal phototherapy on allergic and inflammatory reactions.

#### Other measures

2.6.3

To identify the correlation between the effects of intranasal phototherapy and the cold–heat pattern, we will use the Cold–Heat Pattern Identification Questionnaire. The Cold–Heat Pattern Identification Questionnaire is used to distinguish between cold and heat, which is a characteristic of patients from a Korean traditional medicine perspective. The questionnaire consists of 15 items, which include 8 items related to cold and 7 items related to heat. According to the results of this questionnaire, a patient could be classified as Cold, Hot, neither Cold nor Hot and Cold–Hot complex.^[22]^ The questionnaire will be completed at screening.

### Randomization and allocation concealment

2.7

Participants who meet all inclusion–exclusion criteria will receive a subject identification code. Accordingly, block randomization will be performed to assign the same number of subjects to the medical device or sham device group. A total of 40 participants will be randomly assigned to each group in a 1:1 ratio. A statistician who is not directly involved in the trial will generate a random allocation sequence using a computer program (Strategic Applications Software [SAS], version 9.3; SAS Institute Inc, Cary, NC), and the allocation sequence will be sealed in a consecutively numbered secure envelope. The allocation for each randomization number will be put in individually seal opaque envelopes. Consent will be obtained by a Korean medicine doctor, and all participants will be informed that they will be assigned to one of two groups. After the participants have signed the informed consent form, the envelopes will be opened.

### Blinding

2.8

The participants and investigators will be blinded to the group allocation data, which will only be known to the person in charge of the random allocation. The random allocation table will be kept under lock by Medipert, a contract research organization (CRO) not involved in implementing this study. Both medical and sham devices, seemingly the same, will be repackaged and labeled by the device manufacturer (Optowell Co., Ltd., Jeonju-Si, Korea) according to instructions from Medipert before being delivered to the institution (Woosuk Korean Medicine Medical Center). The subjects will receive intranasal phototherapy with their corresponding device, either the medical device or the sham device, according to their randomization number.

### Sample size

2.9

Since the aim of this study is to determine preliminary feasibility, there will be no sample size calculation. We will conduct a pilot study with 40 participants (20 in the medical device group and 20 in the sham device group) based on the previous pilot study,^[23]^ and we predict that the drop-out rate will be 20%. Thirty-two patients are predicted to complete the study. This sample size is considered to be sufficient to provide power analysis and sample size calculation for subsequent large-scale definitive RCTs.

### Data management

2.10

The investigators will telephone the participants before every visit to promote participant adherence. If participants fail to attend treatment sessions, we will ask for the reasons for the absence and encourage visits through telephone contact.

Regular monitoring will be conducted to control the quality of the data according to the planned protocol and standard operating procedures. Medipert, the CRO of this study, will send a clinical research associate (CRA) to Woosuk Korean Medicine Medical Center every week. The CRA will check whether the trial is being conducted according to the approved protocol and whether the data are adequately recorded. Each participant's contact or identifying information will be separately stored. Personal identity will not be disclosed. Additionally, investigators will not collect any other personal data. All data and records related to the clinical trials will be kept in a locked cabinet. Documents related to this clinical trial should be kept for 10 years after completion of the clinical trial under the supervision of the custodian after completion of the clinical trial result report.

### Safety and adverse events

2.11

The participants will be asked to voluntarily report information about adverse events (AEs), and the investigator will assess any adverse events and vital signs at every visit to monitor the participant's compliance and safety. AEs such as nasal dryness, nasal septum perforation, burning, epistaxis (nosebleed), inflammation or stinging, or other AEs reported during the study period will be recorded on the adverse events form in accordance with the guidelines of the Institutional Review Board. The symptoms, date of occurrence and disappearance, severity, causal relationship with the treatment, other medications or treatments suspected to have caused the AE, and treatment for the AE will be recorded in detail. When severe AEs occur, the investigator will report the event to the Institutional Review Board (IRB) immediately and decide whether to terminate the study. Additionally, adverse events associated with the intervention during the trial will be appropriately handled, and we will provide corresponding compensation according to the insurance policy.

### Statistical analysis

2.12

The statistical analysis will be performed using SAS by an independent statistician who is blinded to the randomized allocation of participants.

All analyses will follow the full analysis set based on the principle of intention-to-treat (ITT); the per-protocol (PP) analysis set will be used for the sensitivity analysis. We will apply the last-observation-carried-forward (LOCF) rule for missing data.

The demographic characteristics and data of both groups will be summarized by means and standard deviations for the continuous variables, and frequencies and percentages will be presented for categorical variables. Differences in baseline between groups will be evaluated by using independent t tests or Mann–Whitney *U* tests for continuous variables and the chi-squared test or Fisher exact test for categorical variables.

Two-sample *t* tests or Wilcoxon rank-sum tests will be used to analyze differences in the primary and secondary outcomes before and after treatment in each group. To demonstrate superiority, we will check whether the upper limit of the one-sided 95% confidence interval (CI) of the difference in the primary outcome between the 2 groups is less than the superiority margin (0.28 points).^[24]^

All participants who participated in at least 1 session will undergo an adverse effect evaluation. All adverse effects reported during the clinical trial will be analyzed. To compare groups and the incidence of adverse events related to the two groups, the chi-square test or Fisher's exact test will be used. The level of significance will be set at 0.05 (2-tailed), except in the case of the primary outcome.

No interim analysis will be performed due to the short duration of the trial.

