## Discussion

3

Due to the limitations of conventional therapies, there is a need to develop alternative treatments for AR. Among them, intranasal phototherapy has received growing interest as an alternative choice to relieve the symptoms of AR patients who cannot take conventional medications because of contraindications or who do not respond well to conventional therapy. Therefore, to investigate the effects and safety of intranasal phototherapy for AR, this proposed trial has been rigorously designed as a randomized, double-blind, placebo-controlled, clinical trial to minimize risks of bias.

In this study, participants will be blinded during the intervention processes using a sham device that is the same in appearance as the treatment device. As the devices will be labeled by the device manufacturer who is not involved in this trial, the investigator operating the device will be blinded to reduce performance bias.

This RCT adopts objective measures such as serum IgE and eosinophil count as well as questionnaires such as the RQLQ to further investigate the mechanisms of action of intranasal phototherapy for AR. In addition, we will utilize the last-observation carried forward (LOCF) rule and intention-to-treat (ITT) approach to manage the attrition bias.

There are some limitations related to the small sample size and lack of sample size calculations. Additionally, we did not stratify demographic factors and characteristics of AR, such as severity and duration of AR, in the randomization process. Therefore, based on the findings of this study, subsequent large-scale definitive RCTs will be needed to confirm the effects and safety of intranasal phototherapy for the treatment of AR.

This protocol was approved by the Korea Food and Drug Administration (KFDA) Investigational Medical Device Application (IMDA). We expect that the results of this study will provide preliminary evidence for broadening the approval range of phototherapy for use in “allergic rhinitis.” Additionally, the results of this study will be the basis for the evaluation of the New Health Technology Assessment (new-HTA).

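### Last observation carried forward is the only missing-data rule: it sets the change in RQLQ, IgE and eosinophils to zero for anyone missing visit 11, dilutes a TNSS effect, and does not manage attrition bias as claimed

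*Protocol article*

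**What the plan says.** The Statistical analysis section of the protocol article gives one rule for missing values: "We will apply the last-observation-carried-forward (LOCF) rule for missing data". The only sensitivity analysis named there is a change of analysis set: "the per-protocol (PP) analysis set will be used for the sensitivity analysis". The Discussion gives the purpose: "we will utilize the last-observation carried forward (LOCF) rule and intention-to-treat (ITT) approach to manage the attrition bias".

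The Sample size section plans "40 participants (20 in the medical device group and 20 in the sham device group", adds "we predict that the drop-out rate will be 20" per cent, and concludes "Thirty-two patients are predicted to complete the study". It expects the data to support the power and sample size calculation of a later definitive trial.

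The measurement schedules differ by outcome:

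- **TNSS (primary):** "TNSS will be measured at every visit".
- **RQLQ:** "The RQLQ score will be assessed twice", at visit 2 before treatment starts and at visit 11 when it ends.
- **Total IgE and eosinophil count:** at screening (visit 1) and at visit 11.
- **Nasal Endoscopy Index:** at every visit.

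**The concern.** LOCF assumes that a participant's score would have stayed where it was last seen. In a two-week treatment trial whose endpoint is change, that is hard to defend.

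For three of the four secondary outcomes nothing is measured between the pre-treatment value and visit 11. The last observation of anyone missing visit 11 is the pre-treatment value, and the imputed change is zero by construction. These outcomes include the two laboratory measures on which the Discussion relies to study mechanism.

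For TNSS the rule freezes a value from part-way through treatment, so it understates the change of those who leave.

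Two things are at stake. The estimated differences and SDs go forward into the design of a definitive trial. The article also tells its readers that the rule controls a bias which it can itself introduce.

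**Working it through.** **1. The plan's own figure.** 40 × (1 − 0.20) = 32 completers, as stated, so 8 drop-outs. The trial has two weeks of treatment and one week of follow-up, and visit 11 ends treatment. Anyone lost in the follow-up week already has a visit-11 value, so 8 of 40 is an upper figure for missing visit-11 data.

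**2. RQLQ, IgE and eosinophils.** Let d be the proportion missing visit 11 in each arm. Imputed changes are 0, so the expected difference is (1 − d) × the true difference, if drop-outs would have changed like completers. At d = 0.20 the retained share is 0.80.

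The variance also changes. With true mean change μ and SD σ within an arm, the variance after imputation is 0.8(σ² + μ²) − (0.8μ)² = 0.8σ² + 0.16μ².

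| Mean change | Variance after LOCF | SD after LOCF |
|---|---|---|
| 0 | 0.80σ² | 0.89σ |
| σ | 0.96σ² | 0.98σ |
| 2σ | 1.44σ² | 1.20σ |

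The SD can therefore be too small or too large.

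**3. TNSS: assumptions.** The article gives no SD, trajectory or drop-out by arm. Assume linear change from visit 2 to visit 11 (nine steps), with the last observed visit of a drop-out uniform over visits 2 to 10. The mean fraction of the change reached is f = (0 + 1 + … + 8)/(9 × 9) = 36/81 = 0.444.

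**4. TNSS: equal drop-out with a true effect.** Retained share = 1 − 0.20 × (1 − 0.444) = 0.889. A true difference of 2.0 points is estimated as 2.0 × 0.889 = 1.78.

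**5. TNSS: no true effect.** If both arms change by C, the bias (active minus sham) is C × (1 − f) × (d_sham − d_active), where 1 − f = 0.556.

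| Drop-out, active v sham | C = −2 | C = −3 | C = −4 |
|---|---|---|---|
| 20% v 20% | 0 | 0 | 0 |
| 15% v 25% | −0.11 | −0.17 | −0.22 |
| 10% v 30% | −0.22 | −0.33 | −0.44 |
| 30% v 10% | +0.22 | +0.33 | +0.44 |

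The bias favours the arm that loses fewer participants. For comparison with the 0.28-point margin:

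- At 10% v 30% the bias is 0.556 × 0.20 = 0.111 per point of common improvement. It exceeds 0.28 only when that improvement is above 0.28/0.111 ≈ 2.5 points.
- At 15% v 25% it is 0.056 per point, and the improvement would have to exceed about 5 points.

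**6. Check by simulation.** With 20 per arm, 40,000 trials, C = −3 and an assumed SD of change of 3, the mean null difference was −0.01 at 20% v 20%, −0.34 at 10% v 30% and +0.33 at 30% v 10%. A nominal 5% one-sided test against zero rejected in about 5%, 10% and 2% of trials. These rates are for a test against zero, not for the plan's rule, which compares a one-sided confidence limit with 0.28.

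**The case against.** The strongest case against concerns size, and most of it stands.

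- **LOCF is not wrong whenever symptoms change.** A reader might infer that it is. At equal drop-out unrelated to outcome the null comparison is unbiased, and a true effect is diluted, which is conservative for a superiority claim.
- **No imbalance in drop-out is predicted.** The trial is double-blind with devices of identical appearance, and participants are telephoned before each visit. The 10% v 30% case means 2 v 6 of 20, and nothing in the article forecasts it.
- **Eight missing values are not the expected number.** The 20% is drop-out from the whole study, follow-up week included.
- **The 80% figure is conditional.** If drop-outs had half the completers' effect, the true difference over all participants would be 0.8 + 0.2 × 0.5 = 0.9 of the completers' effect, and the retained share 0.8/0.9 = 0.89. If they had none, nothing would be lost.
- **Per-protocol may help a little.** The article does not define that set. If it leaves out those who miss visit 11, comparing it with LOCF is an imperfect check.
- **This is a 40-participant pilot**, and a battery of missing-data analyses would be out of proportion.

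Two things survive. The zero change for twice-measured outcomes follows from the schedule alone, without any modelling. And the article does not leave the method to an analysis plan: it fixes LOCF and gives it a purpose that it does not serve. A per-protocol analysis changes who is analysed; it does not vary the assumption about missing values.

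**Conclusion.** The point holds, with its size stated as conditional. For RQLQ, total IgE and eosinophils, LOCF is baseline carried forward. Up to 8 of 40 changes would be set to zero. With 20% missing in both arms, about 80% of a true difference remains if drop-outs would have changed like completers, and the SD passed to the definitive trial is distorted.

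For TNSS, about 89% of a true effect remains at equal 20% drop-out. Without a true effect, the comparison is biased only if the rate or timing of drop-out, or its relation to outcome, differs between arms. For a common improvement of 2 to 4 points, the bias is about 0.11 to 0.22 points at 15% v 25% and 0.22 to 0.44 at 10% v 30%. These figures rest on assumed linear change and uniform drop-out times and are illustrative.

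A reader might go further and conclude that the primary result is expected to shift by more than the 0.28-point margin, or that its type I error is inflated. The article does not support this. It predicts no imbalance, most of the range shown lies below 0.28, and the simulated error rates do not test the plan's own decision rule.

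The matter should be put right, but it is not fatal to a pilot.

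**What to change.** 1. **TNSS:** use a likelihood-based repeated-measures model on all observed visits, with baseline, arm, visit and arm-by-visit. Because the sample is small, group the visits or use a structured covariance, chosen in advance. Read the arm contrast at visit 11 and apply the stated one-sided confidence-limit rule to it.
2. **RQLQ, IgE and eosinophils:** use baseline-adjusted models on observed visit-11 values, or multiple imputation.
3. **LOCF:** keep it only as a sensitivity analysis.
4. **Discussion:** delete the statement that LOCF manages attrition bias.

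The cost is revised wording and slightly more programming. No extra data are needed, since TNSS is already recorded at every visit. The drawback is that the TNSS model needs a covariance choice at small sample size.

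### The primary comparison of TNSS change is not adjusted for baseline TNSS; it is valid, but less precise than an ANCOVA using data already collected

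*Protocol article*

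**What the plan says.** All references are to the protocol article.

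- **Endpoint (Primary outcome):** "The primary outcome is the change in the Total Nasal Symptom Score (TNSS) from baseline to 2 weeks". The same section adds that "TNSS will be measured at every visit, and we will analyze the differences in effects between groups", so a pre-treatment value exists for each patient.
- **Test (Statistical analysis):** "Two-sample *t* tests or Wilcoxon rank-sum tests will be used to analyze differences in the primary and secondary outcomes before and after treatment in each" of the two arms.
- **Decision rule (Statistical analysis):** the "upper limit of the one-sided 95% confidence interval (CI) of the difference in the primary outcome between the 2 groups" is set against a margin of 0.28 points. Other tests are two-sided: "The level of significance will be set at 0.05 (2-tailed), except in the case of the primary outcome".
- **Baseline data (Statistical analysis):** "Differences in baseline between groups will be evaluated by using independent t tests" or Mann–Whitney U tests for continuous variables. No later step uses the results of these tests.
- **Randomisation (Discussion):** among the limitations, "we did not stratify demographic factors and characteristics of AR, such as severity and duration of AR, in the randomization process".

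No covariate, ANCOVA or other adjusted model appears anywhere in the article.

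**The concern.** With 20 patients per arm and no stratification on severity, the arms can differ by chance in baseline TNSS. Taking the change from baseline does not remove the effect of that difference. Unless rho is 1, patients who start higher tend to fall further through regression to the mean, so the arm that starts worse tends to look as if it improved more. Testing the baseline difference for significance does not correct this either.

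An analysis that includes baseline TNSS as a covariate removes the linear part of the effect and usually gives a narrower interval. At stake are the width of the interval behind the one-sided decision rule and the quality of the estimate that, according to the Sample size section, should inform the definitive trials.

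**Working it through.** **Inputs from the article.** 40 patients, 20 per arm; 20% predicted drop-out; full analysis set with last observation carried forward; one-sided 95% limit for the primary outcome.

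**Inputs that are assumptions.** The article gives no SD and no correlation for TNSS. I take rho from 0.3 to 0.9, equal variances at baseline and week 2, and express effects in units of the TNSS SD at one visit.

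**1. The article's own figure.** 40 x (1 - 0.20) = 32 completers. This reproduces. It is the only sample-size arithmetic given; no power or effect size is stated.

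**2. Size of chance imbalance.** The SD of the difference in baseline means is sqrt(2/n).
- n = 20 per arm: 0.316 SD, so P(|difference| > 0.3 SD) = 34%.
- n = 16 per arm (completers): 0.354 SD, and 40%.

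The main analysis uses the full analysis set with imputation, so 34% is the relevant figure.

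**3. What an imbalance does to the change score.** Let d be the baseline difference, device minus sham. With equal variances the expected week-2 difference is effect + rho x d. Subtracting d gives effect - (1 - rho) x d. For d = 0.3 SD:
- rho 0.3: -0.21 SD
- rho 0.5: -0.15 SD
- rho 0.7: -0.09 SD

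**4. Precision.** Per patient, Var(change) = 2s²(1 - rho) and Var(ANCOVA) = s²(1 - rho²), so the ratio is (1 + rho)/2. Estimating the slope multiplies this by 1 + 1/(N - 4), which is 37/36 at N = 40 and 29/28 at N = 32.

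| rho | (1 + rho)/2 | N = 40 | N = 32 | 40 patients act like |
|---|---|---|---|---|
| 0.3 | 0.65 | 0.67 | 0.67 | about 60 |
| 0.5 | 0.75 | 0.77 | 0.78 | about 52 |
| 0.7 | 0.85 | 0.87 | 0.88 | about 46 |
| 0.9 | 0.95 | 0.98 | 0.98 | about 41 |

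At rho 0.5 and N = 40, with t quantiles on 37 rather than 38 degrees of freedom, the interval is about 12% narrower. Break-even is where the ratio reaches 1: rho = 72/37 - 1 = 0.95 at N = 40, and 56/29 - 1 = 0.93 at N = 32.

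**5. Does the direction depend on equal variances?** Before the slope cost, no. With SDs b at baseline and y at week 2, Var(change) - Var(ANCOVA) = (b² + y² - 2 rho b y) - y²(1 - rho²) = (b - rho y)², which is never negative. Only the size of the gain depends on that assumption.

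**6. Simulation check.** 10,000 trials per setting, N = 40, assumed true effect 0.7 SD, one-sided 0.05 test against zero. Power for change score and ANCOVA was 58% and 74% (rho 0.3), 70% and 80% (rho 0.5), 87% and 91% (rho 0.7), and above 99% for both at rho 0.9. The simulated variance ratios (0.67, 0.77, 0.88, 0.97) agree with the table.

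**The case against.** The strongest reply is that nothing is invalid here. Under randomisation the unadjusted change-score comparison is unbiased, and its interval already allows for chance imbalance. The shift is also modest: at rho 0.5 the standard error of the change difference with 20 per arm is sqrt(2 x 0.5) x sqrt(4/40) = 0.316 SD, so 0.15 SD is about half a standard error. **This stands.** The point concerns efficiency and the estimate given the imbalance that occurs, not validity.

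The gain may also lie at the low end. Large stable differences between patients would raise rho, and so would carrying early values forward for drop-outs. **This stands too**, and is why the range runs to 0.9, where about 2% is gained.

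It could also be said that the unseen analysis plan may contain an adjusted model. It may add one as support, but the article itself names the test and the decision rule, so the unadjusted comparison is a stated choice.

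A reader might infer more than the article supports:
- *Baseline TNSS is used only in the baseline tests.* It also enters by subtraction in the endpoint, and the sentence on baseline tests does not name TNSS.
- *A large imbalance is likely.* At 34% for more than 0.3 SD, most trials would stay below that level. No baseline distribution is given, so wide variation in TNSS cannot be assumed.
- *The main analysis is within-group, because the sentence ends with each group.* The two-sample tests, the between-group interval and the Primary outcome section all point to a comparison between arms.
- *The baseline tests damage the analysis.* They are redundant, but no stated analysis depends on them.

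**Conclusion.** The point holds as one of efficiency. The article fixes an unadjusted comparison of TNSS change although the covariate that would sharpen it is already collected. With 40 patients, adjustment cuts the variance of the treatment effect by about 33%, 23%, 13% or 2% at rho 0.3, 0.5, 0.7 or 0.9, and would lose slightly only above about 0.95 (0.93 with 32). These sizes rest on assumed correlations and equal variances; the article cannot settle them.

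The documents do not support calling the planned test biased or invalid. Nor would ANCOVA cure every imbalance: it removes the linear effect of baseline TNSS, not differences in other factors such as duration of disease. The change is worth making because it answers, for severity as measured by TNSS, a limitation that the authors raise themselves.

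**What to change.** Before unblinding, specify the primary analysis as an ANCOVA of week-2 TNSS (or, equivalently for the treatment effect, its change) on arm with baseline TNSS as covariate. Take the one-sided 95% limit for the decision rule from that model, and keep the rank-sum test as a sensitivity analysis.

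Use the same approach for the continuous secondary outcomes, each with its own baseline: RQLQ, log IgE and log eosinophil count. The Nasal Endoscopy Index is described by categorical aspects, so a linear ANCOVA should not be extended to it without first checking that it suits the scale.

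Keep the descriptive baseline table; dropping its p-values is optional.

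The cost is a sentence or two in the plan and one degree of freedom. No extra data or patients are needed.
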